### Expected outcomes and limitations

We expect participants to have significant reduction in EDC levels after the report-back and intervention with a greater effect in the intervention group. We may experience a bias towards the null if users are actively trying (or begin trying) to reduce EDC exposures at the start of the study. This potential issue will be addressed by examining the EHL and readiness to change surveys, to assess any previous or ongoing EDC reduction activity. In previous work, EHL was high in participants at baseline [44]. This was due to the insensitivity of the survey for EDC-specific EHL. We have since modified our EHL survey to specifically assess EDC EHL knowledge, attitudes, and behaviors, and will utilize this modified EHL survey in the current proposal. In terms of quality control of lab analyses, LCMS can have technical issues known as batch effects and inefficient compound identification. We will minimize batch effects by taking several cautions: 1) samples will be collected as described in a Standard Operational Protocol and stored at -80^o^C until analysis; 2) all samples will be analyzed in a single batch for each LCMS setup to eliminate batch variation; 3) standard mixture of known benchmark metabolites will be analyzed within each batch at multiple time points to control for fluctuation in instrument performance; and 4) technical blank samples are included periodically throughout sample collection to control for variation in sampling. To overcome identification inefficiency, we will use post-acquisition strategies such as running available standards and representative samples to identify unannotated metabolites that are differentially expressed over time with high confidence. The resulting elution time and mass fragmentation pattern will be used as evidence of the potential chemical identity of unannotated metabolites. The analytical laboratory will also provide additional analysis data including target retention time (RT), target response, surrogate RT, surrogate response, surrogate RT, surrogate concentration, internal standard RT, internal standard response, date received and analyzed for potential troubleshooting. If any kits/samples are lost in transit, participants will be sent a new kit. The study team will communicate on a regular basis to ensure any problems that arise will be addressed in time, and the study will be conducted with the highest rigor. The biomarker assessment is exploratory, and it is possible we will face unexpected challenges, such as difficulty recruiting people to take the blood test. We will address these issues as they arise, adjusting our approach as needed.

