
These EDCs have relatively short half-lives in the body (i.e. 6 hours to 3 days) [41–43]. Therefore, the fact that most of the population is exposed at any one time [5, 6] indicates ubiquitous and constant exposure sources. However, the rapid elimination from the body also allows for reduction of internal exposure with removal or avoidance of the exposure sources from daily life. Thus, interventions aimed at identifying exposures (through internal and external assessments) and removing them (via personalized recommendations based on exposure levels and lifestyle habits), have the potential to greatly reduce transient EDC exposures, as demonstrated in our previous work [44].

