### Previous work

In previous work, [44] participants in the Healthy Nevada Project completed EHL and readiness to change surveys before (*n* = 424) and after (*n *= 174) an EDC exposure report-back intervention (measured via the MM mail-in testing kit). Report-back of results included urinary levels, information about health effects, sources of exposure, and personalized recommendations to reduce exposure. Participants ranged in age from 18-61, were primarily women (75%), and white (79%). EHL was generally very high at baseline. Higher EHL knowledge was shown among older participants (*p* = 0.02) and those self-rated in poorer health (*p *= 0.007). EHL behaviors increased after report-back (*p *= 0.003).

For readiness to change, 72% were already or planning to change their behaviors. Women were generally in earlier stages than men (p=0.071), but post-intervention, women increased their readiness (p=0.053), while men decreased (p=0.007). When asked what challenges they faced in reducing exposure, 79% cited not knowing what to do. This dropped to 35% after report-back. Participants with higher propylparaben were younger (p=0.03), women and participants who rated themselves in better health had higher levels of some phthalates (p=0.02-0.003 and p=0.001-0.003 respectively). After report-back, monobutyl phthalate decreased among the 55 participants who submitted a second urine test (p<0.001). Of the 50 participants who completed final surveys, 50% reported now using non-toxic personal products, 44% were using non-toxic household products, 20% dined out less, 32% ate less packaged food, 40% used less plastic, and 48% read product labels more.

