## Methods

### Study design

This study is an ongoing collaboration between Million Marker and the Healthy Nevada Project (MM-HNP Study). We will test and compare the effectiveness of 1) EDC exposure report-back (control), and  2) a self-directed online interactive curriculum of EDC EHL material, with access to live coaches and an online forum (intervention). We hypothesize that the self-directed online interactive curriculum with personalized and community support will be more effective (superior) than EDC report-back alone at reducing EDC exposures (behavior change and metabolite concentrations), as well as increasing EDC-specific EHL, readiness to reduce exposures, and well-being. These two arms will be tested in a longitudinal EDC randomized control trial (n=600). Participants will be allocated to intervention groups by the MM team via block randomization, using random-number generation software. The HNP team will generate the allocation sequence and enroll participants. Outcomes for this aim will measure surveyed changes pre- post-interventions in EDC EHL, including EDC-specific knowledge/behavior/attitudes, RtC, well-being, and urine EDC metabolite concentrations. Additionally, we will test a subset of individuals from each intervention arm (*N* = 150 from each group, for a total of
*N* = 300) for clinical biomarkers using a mail-in blood card test. Outcome assessors and data analysts will be blinded to the intervention status of the participants. Additionally, participants will not be aware of their intervention status (i.e. what the other group undergoes).

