### Intervention design

Upon consenting and randomization, all participants will be sent baseline surveys and test kits (for baseline urinary exposure levels, and, for a subset, clinical biomarkers). The control group (n = 300) will complete post-test surveys and use the second kits approximately 3 months after the baseline assessment, while the intervention group (n = 300) will complete a Lifestyle Audit and engage in the 8-week curriculum described above. The intervention group will submit the kits 2 weeks after completion of the curriculum (i.e. 3 months after the baseline test). See Fig. 1 for the control vs. intervention group study events.

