For the analysis plan, we will examine the distribution and concentrations of each of 13 chemical analytes in urine to determine geometric means, medians, percentiles and ranges of exposures. We will compare the percentiles with those reported in the NHANES study. We will include BMI, age, gender, diet, education and household income as covariates. Participants’ dietary patterns will be captured prior to sample collection by looking at their consumption of packaged food and times eating out as these are important culprits of EDC exposures. We will conduct an intent-to-treat analysis. The primary outcomes are the pre-post (first and second tests) differences in specific gravity-adjusted concentration levels per analyte. Clinical biomarkers measured before and after the intervention will also be compared to assess improvement in health and reduced disease risk. We willassess changes in participants’ EHL, RtC and well-being before and after the interventions as well. We will first generate summary statistics on participants’ responses. Changes will be calculated based on paired values of individual responses.

For all analyses, data will be reviewed to ensure assumptions are not violated. If outcomes are not sufficiently normally distributed for parametric tests to be valid, nonparametric tests will be conducted. If needed, variables with response categories with too few participants will be combined. Attrition analyses will be run to compare demographic variables between participants who completed post-test surveys and those who did not.

Summary data and associations between demographic variables and EHL, RtC, well being, EDC metabolites, and clinical biomarkers will be analyzed for all participants with pre-test survey data. Independent sample t-tests, one-way ANOVAs, Chi-square tests, and Spearman’s rank correlations will be run as appropriate. Changes from pre-test to post-test comparing differences between the intervention and control groups, will be analyzed for participants who completed both surveys using regression analyses, controlling for significant demographic variables.

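### Examining the EHL and readiness surveys can describe early exposure reduction but cannot correct a baseline sample it has already lowered, so within-arm change may be understated

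*Protocol article*

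**What the plan says.** All places are in the protocol article.

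- **Expected outcomes and limitations** names the risk, which it places at study entry: "We may experience a bias towards the null if users are actively trying (or begin trying) to reduce EDC exposures". The response follows: "This potential issue will be addressed by examining the EHL and readiness to change surveys", with the purpose of assessing previous or ongoing reduction activity.
- **Data collection, management, and analysis** sets the endpoint: "The primary outcomes are the pre-post (first and second tests) differences in specific gravity-adjusted concentration levels per analyte". It also plans the comparison of arms: "Changes from pre-test to post-test comparing differences between the intervention and control groups, will be analyzed" by regression in participants who completed both surveys.
- **Study design** gives the hypothesis that the curriculum "will be more effective (superior) than EDC report-back alone at reducing EDC exposures".
- **Intervention design** gives the order of events: "Upon consenting and randomization, all participants will be sent baseline surveys and test kits".
- **The Millon Marker (MM) test kit and report-back** gives the intervention arm a coach call with a Lifestyle Audit on the day before the urine collection. The control arm skips that step.
- **Need for EDC intervention** gives half-lives of 6 hours to 3 days.
- **Previous work** reports that in the earlier study "72% were already or planning to change their behaviors".

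**The concern.** The article claims that a bias it has identified will be dealt with, and the tool it names cannot do that. A questionnaire can sort participants by what they were already doing. It gives no information on the urine level they would have had otherwise.

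The sequence of events gives room for the problem. The consent text (Participants) warns that results may reveal high exposure with possible harm to health. The survey items (Surveys, study measurements and secondary outcomes) mention harmful chemicals in dust and purchased products, and the surveys go out with the kit. With short half-lives, a change made between consent and the first void can show in the baseline sample.

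Two quantities are at stake, and they behave differently. The first is the within-arm pre-post change. Both arms receive report-back, so the article's claims about report-back as such can rest only on this change. Those claims are the biomarker hypothesis in Clinical biomarker testing, the expected reduction in Expected outcomes and limitations, and the effectiveness statement in Discussion. The second is the randomised contrast, which is affected only under further conditions.

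**Working it through.** The plan gives no figure for this bias, so there is none to reproduce. Neither the size of an early cut nor the share of participants making one is given. Both are assumed below.

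**Step 1. Can a recent change reach the baseline urine?** The fraction of the way to the new steady state after time t is 1 − 0.5^(t/half-life), with the article's two half-lives:

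- 6 h half-life: 24 h gives 1 − 0.5^4 = 0.94; 7 days gives 1.00.
- 72 h half-life: 24 h gives 1 − 0.5^(1/3) = 0.21; 7 days gives 1 − 0.5^(168/72) = 0.80.

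For an assumed 30% cut in intake, the baseline is too low by 28% or 6% at 24 h (6 h or 72 h half-life), and by 30% or 24% at 7 days. Suppose the participant's lasting reduction is the same 30%, all of it begun before the void, which is the worst case. The measured fall is then:

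- 24 h: 1 − 0.70/0.72 = 3% and 1 − 0.70/0.94 = about 25%.
- 7 days: 1 − 0.70/0.70 = 0% and 1 − 0.70/0.76 = 8%.

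The true fall is 30%. This concerns one such participant, not the trial average.

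**Step 2. What happens to the arm-level results?** Assume true reductions of 10% (control) and 30% (intervention), so the true between-arm reduction is 1 − 0.70/0.90 = 22.2%. A share p cuts by 20% before baseline and ends at the same final level as otherwise. On geometric means, the observed within-arm ratio is (1 − true reduction)/0.8^p, where 0.8^p is 0.956, 0.894 and 0.852 for p = 20%, 50% and 72%.

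| Share p | Control, within-arm fall | Intervention, within-arm fall | Between arms: p in both | Between arms: p in intervention only |
|---|---|---|---|---|
| 0% | 10.0% | 30.0% | 22.2% | 22.2% |
| 20% | 5.9% | 26.8% | 22.2% | 18.7% |
| 50% | −0.6% | 21.7% | 22.2% | 13.0% |
| 72% | −5.7% | 17.8% | 22.2% | 8.7% |

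For example, at 20% the control fall is 1 − 0.90/0.956 = 5.9%. With p in both arms, 0.8^p divides out of the contrast. With p in the intervention arm only, the contrast is 1 − (0.70/0.956)/0.90 = 18.7%. A simulation with 400,000 per arm agrees to within 0.3 percentage points.

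**Step 3. Does adjusting for baseline help?** Take log-scale standard deviations of 0.7 between persons and 0.7 within persons. In the intervention-only case, the simulated baseline-adjusted contrast is 20.5%, 17.9% and 15.7% for the three shares. The bias is smaller but remains.

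**Step 4. Early reducers with less left to gain.** If cutters in both arms keep at least their own 20% cut, the contrast is 20.4%, 17.6% and 15.4%. This is a smaller real difference between the arms, because control cutters end lower. It is not an error caused by the lowered baseline.

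**The case against.** The strongest reply is that the trial's question is the randomised contrast, and a cut common to both arms cancels there. That stands, as the fourth column of the table shows. A reader might infer that the primary treatment effect is understated. The documents do not support that: the article says only that bias may occur, and nothing in it shows that early reduction is unequal between arms.

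Further points for the plan also stand in whole or part:

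- A participant who had changed habits before enrolment has a true baseline. Only those who begin between consent and the void fit the mechanism, and for the former group a survey is a sensible tool.
- A reader might take the 72% from Previous work as the affected share. It pools people already acting with people planning to act, in an earlier study, and does not estimate how many begin in that window.
- A reader might also infer that the surveys play no part in the metabolite analysis. Surveys, study measurements and secondary outcomes does plan an association of EHL and readiness with EDC levels. Data collection, management, and analysis relates diet and product use to change in exposure. These analyses describe; they do not restore a baseline. Neither covariate list in that section names EHL or readiness.
- The audit records food and products used, and recommendations come only with the results. Much of that day's exposure may precede the call. The audit also appears to be repeated with the second kit, so a reaction to it could partly offset in the difference. The arm-specific route is therefore possible, not shown.
- The kit card and full consent materials are not shown and may already ask participants to keep usual habits. If so, the article should cite that instruction instead of the surveys.

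**Conclusion.** The point holds in a limited form. Examining surveys describes early reduction and does not correct for it, so saying the issue will be addressed claims too much. Within-arm pre-post change may be understated, and this matters for the statements about report-back itself, where no randomised comparison is available. The between-arm contrast may be biased only if early reduction differs by arm. The order of randomisation, audit and baseline void makes that possible. The direction would probably be towards the null, because the intervention arm's baseline would be the one lowered, which works against the superiority claim.

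The size is unknown. The figures above rest on assumed cuts of 20% or 30%, assumed true reductions and assumed shares. They show how the bias behaves and do not forecast it. No sample-size figure in the article is affected.

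**What to change.** 1. In The Millon Marker (MM) test kit and report-back and in Intervention design, tell both arms to keep their usual products and diet until the baseline void. Put this on the kit card, in the kit email and, for the intervention arm, in the audit call.
2. Release the baseline surveys and educational material only after that void and before results are returned.
3. Record at kit activation whether habits changed since the invitation, and report the answers by arm as a descriptive check.
4. In Expected outcomes and limitations, say that the surveys describe this bias and do not correct it.

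Two analytic remedies are not recommended. An arm-by-readiness interaction would not restore a lowered baseline. Excluding self-reported changers conditions on an answer given after randomisation, so the remaining subset should not be presented as a randomised comparison.

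The cost is one line of instruction, a changed order of emails and one question. Surveys arrive slightly later and, in the intervention arm, would follow the audit call, so any effect of that call on the answers enters the survey baseline. Recruitment is in staggered waves that have already begun (Trial status). Earlier waves keep the old order, so results should also be reported by wave. The audit stays before the baseline void, so the instruction reduces the arm-specific route without removing it.

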## Intervention

### The Millon Marker (MM) test kit and report-back

The MM EDC testing panel consists of 13 metabolites, assessing exposure to EDCs that are commonly found in household and personal products. These chemicals are found in over 90% of the US population (at any one time) [5, 15, 21, 22, 62].

Consented participants will be mailed the MM *Detect and Detox* kit. Upon receipt, participants in the intervention group will 1) engage in a Zoom call with a MM coach to complete a comprehensive 24-hour food/product Lifestyle Audit the day before their urine sample collection, 2) collect first void urine sample the next morning, 3) send back samples via FedEx, 4) receive results as well as personalized recommendations for products and lifestyle changes to reduce EDC exposures, 5) follow the recommendations and make changes to reduce exposures, 7) test again after 3 months. Participants in the control group will complete Steps 2-7, and will receive a report-back with more generalized recommendations. Participants will be guided through this journey from our online instructions, online video tutorials, extensive educational materials, and email communication.

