**Fig. 1 Fig1:**
[figure not shown]
Timeline of study events for control and intervention groups

Participants will be able to view the results of their Lifestyle Audit online, as well as their test results and reports. These tools will also help participants to self-monitor their behaviors and exposure reduction progress. All participants (control and intervention) will receive a report back of their urinary exposure levels. The control group will receive a list of general recommendations for exposure reduction based on their EDC exposure levels,while the intervention group will receive a more personalized exposure reduction plan based on the information collected in their Lifestyle Audit.

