### Data collection, management, and analysis

The MM *Detect and Detox* kit is an at-home sample collection service that participants will use to collect their own samples. The mailed kit has the following components: kit box, instruction card with activation code, sterile urine collection cup, biohazard bag with absorbent paper, pre-labeled polymailer. We have built a secure online portal for users to make accounts, register their kits, track the status of their samples, and view their testing results and feedback online. For the Lifestyle Audit, participants in the intervention group will schedule a Zoom call with a MM lifestyle coach to document the food, drinks they consumed, as well as all the products (personal care and household products) they used on the day prior to urine collection. MM’s technology team will oversee the security of MM’s software stack and servers, ensure that the platform is HIPAA-compliant, and oversee the software building and maintenance for this project.

Several emails will be sent to the participants to update them on their sample and report statuses and keep them engaged. FedEx Priority Overnight shipping will be used to ensure the sample quality. The turnaround time for the lab analysis and MM report generation is 2-4 weeks. Three months after submitting their baseline urine sample, participants will be sent the second kit and go through the same process again and submit their second samples. Detailed flow of events is illustrated in Fig. 1.

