### Trial status

Recruitment of HNP participants to this study beganJuly 2024, with subjects being recruited into study waves with staggered starts for ease of recruitment and data collection. The initiation of study events began as the first wave of participants was recruited, September 2024.

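### The single-batch claim for the urine assays cannot hold alongside 2-4 week report-back and a 3-month retest, so between-run variation is reduced but not eliminated

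*Protocol article*

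**What the plan says.** All places are in the protocol article.

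- **Batch claim** (Expected outcomes and limitations): among four precautions against batch effects, "all samples will be analyzed in a single batch for each LCMS setup to eliminate batch variation". Samples are to be held frozen until analysis: "samples will be collected as described in a Standard Operational Protocol and stored at -80" °C. The next precaution in the list runs benchmark standards within each batch.
- **Turnaround** (Data collection, management, and analysis): "The turnaround time for the lab analysis and MM report generation is 2-4 weeks".
- **Report before retest** (The Millon Marker (MM) test kit and report-back): participants "receive results as well as personalized recommendations for products and lifestyle changes to reduce EDC exposures", act on them, and test again after 3 months. The control arm's recommendations are more general, but "All participants (control and intervention) will receive a report back of their urinary exposure levels" (Intervention design, text after Fig. 1).
- **Second sample** (Data collection, management, and analysis): "Three months after submitting their baseline urine sample, participants will be sent the second kit". For the intervention arm, Intervention design says: "The intervention group will submit the kits 2 weeks after completion of the curriculum (i.e. 3 months after the baseline test"). The same section puts the control arm at approximately 3 months after baseline.
- **Waves** (Trial status): recruitment proceeds "with subjects being recruited into study waves with staggered starts for ease of recruitment and data collection".
- **Primary outcome and covariates** (Data collection, management, and analysis): the primary outcome is the pre-post difference per analyte after specific gravity adjustment. The covariates named there do not include batch, run date or wave.

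**The concern.** The batch sentence claims a property of the primary measurement that the rest of the design rules out. The baseline report is the control condition and part of the intervention, so the baseline assay cannot wait for the follow-up urine. The first and second samples of any one person must come from different runs.

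This matters because the primary outcome is a within-person difference between those two samples. A calibration difference between the runs goes straight into that difference and looks like a change in exposure. Both arms receive report-back, so no arm shows what would happen without it. The article nevertheless expects reductions after report-back in both arms (Clinical biomarker testing; Expected outcomes and limitations), and the Discussion says the study will demonstrate that report-back is effective. Those statements rest on within-arm pre-post change, the quantity most exposed to a between-run shift.

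Because the text treats batch variation as eliminated, it gives no rule on how the arms are placed across runs.

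**Working it through.** **1. Timeline check.** The article gives no figure to reproduce here, so the check is on its own dates. Three months is taken as about 13 weeks.

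- Baseline result reported: weeks 2-4.
- Second kit sent: about week 13.
- Gap between the end of baseline analysis and the existence of the follow-up sample: 13 − 4 = 9 to 13 − 2 = 11 weeks.
- Intervention arm: report 2-4 weeks + 8-week curriculum + 2 weeks = 12-14 weeks, which agrees with the stated 3 months.

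Each participant therefore needs at least two assay occasions. With W waves there are up to 2W if each wave and time point is run separately; W is not given. One run could hold both samples only if stored baseline aliquots were re-assayed with the follow-up samples, which the article does not mention.

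**2. Could the qualifier about each LCMS setup rescue the sentence?** If it means each instrument run, the step is feasible, but it then says nothing about variation between runs and cannot eliminate it. If it means one batch for the whole trial on each method, the timeline forbids it. The claim fails on both readings.

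**3. Effect on within-arm pre-post tests (illustration).**

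Inputs: n = 150 per arm after attrition (Sample size). Assumed, because the documents do not give them: log-scale SD 1.0 at each time point, within-person correlation r = 0.4, no true change, and a residual downward shift s left after the laboratory controls.

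- SD of log change = √(2 × (1 − 0.4)) = 1.095
- Standardised shift dz = −ln(1 − s) / 1.095
- Noncentrality = dz × √150, referred to a two-sided 0.05 paired t-test

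| Shift s | −ln(1 − s) | dz | dz × √150 | False-positive rate |
|---|---|---|---|---|
| 5% | 0.051 | 0.047 | 0.57 | about 9% |
| 10% | 0.105 | 0.096 | 1.18 | about 22% |
| 15% | 0.163 | 0.148 | 1.82 | about 44% |
| 20% | 0.223 | 0.204 | 2.49 | about 70% |

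Sensitivity: for upward shifts, ln(1 + s), with the SD of log change varied from 0.8 to 1.3, the rates are 7-12% for a 5% shift, 15-31% for 10% and 40-79% for 20%.

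**4. Effect on the between-arm contrast.** If a fraction p of each arm's follow-up samples falls in the shifted run, the bias in the difference in log change is ln(1 + s) × (difference in p between arms).

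- Equal shares: the bias is 0, because the shift cancels.
- A 25-point difference in shares (assumed): exp(0.25 × ln(1 + s)) − 1 = 1.2%, 2.4% and 4.7% for shifts of 5%, 10% and 20%.

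**The case against.** The strongest reply is that the batch sentence is only one of several precautions. Every target is quantified as a ratio to an isotope-labelled surrogate added before preparation. An internal standard, duplicate runs, blanks and per-batch benchmark standards are also stated. A reader might infer that the plan makes no adjustment for batch at all; the documents do not support that. These measures act on run-to-run drift and should make any residual shift small. They do not make it zero, and they do not make the sentence true.

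Three further points stand in whole or part.

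- **The randomised contrast.** The stated hypothesis is superiority over report-back alone, tested on between-group differences in change. A shift common to both arms cancels there, so the false-positive rates in the working do not apply to it.
- **Arm timing.** A reader might infer that the arms retest on different schedules and so fall in different runs. The text puts both at about 3 months; only the trigger differs (curriculum completion against calendar). Imbalance by arm is possible but not established.
- **Full confounding.** A reader might infer that batch and time point are inseparable across the whole trial. They are separated by run for each participant, but one wave's follow-up samples could share a run with a later wave's baselines. Wave spacing is not given, so this cannot be settled.

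A batch or run-date term may also sit in the statistical appendix, which is not shown, so its absence from the article is not counted as a fault.

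**Conclusion.** The concern holds in limited form. The single-batch statement is wrong as written: report-back and the 3-month retest alone force separate runs for each participant's two samples, and the staggered waves add to this. Between-run variation is reduced by the stated laboratory controls but not eliminated, and for each participant it coincides with time point in the primary pre-post difference.

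The consequence falls mainly on within-arm claims of reduction. Under the stated assumptions their false-positive rate rises from 5% to about 9-70% for residual shifts of 5-20%. The documents give neither the shift nor the log-scale SD and correlation, so these are illustrations, not estimates; after surrogate-ratio quantification the lower end may be the more relevant.

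The between-arm comparison is largely protected provided both arms share runs. The article does not say that they do. Even with a 25-point imbalance, the bias is about 1-5% for shifts of 5-20%. The point should be corrected, because the text asserts a safeguard that cannot operate and the remedy is cheap.

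**What to change.** 1. Replace the single-batch sentence with a run-allocation rule: at each time point, samples from both arms of a wave are run together in random order, with a common control sample carried across all runs.
2. Include wave or run date in the primary between-arm model, if the statistical appendix does not already do so. The laboratory already returns the date of analysis with each result, so no new data are needed.
3. Base the effect conclusion on the between-arm difference in change. Report unadjusted within-arm change as descriptive, not as evidence that report-back reduces exposure.

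Cost: a run-order instruction to the laboratory, one control material and one model term. The downside is that some samples are held for a few days to fill a two-arm run, which should fit within the 2-4 week turnaround.
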